### Data collection and management

A data collection notebook (CRD) will be compiled with all the variables described. Patients will arrive at the operating room with the first sheet completed (including demographic, analytical, respiratory function, and preoperative morbidity information). During surgery, intraoperative information will be collected on the subsequent pages. Before registration, the CRD pages corresponding to the patient’s stay in the PCU will be filled out. The CRD information will be completed before discharge. The CRD will include the patient’s in-hospital medical history and information that is not computerized. At the time of discharge, it will be kept in a locked cabinet in the anesthesiology department and will be completed with the data obtained during the day-30 visit. Data from the CRDs will be entered into the computer program SPSS, where they will be reviewed and accepted by an external clinical research organization (CRO). This CRO will ensure compliance with the study procedure and will control the possible errors that may occur.

The criteria for withdrawal from the study are as follows:
The protocol procedures cannot be followed for medical reasonsTransfusion of intraoperative blood productsDuration of OLV less than 60 minAdverse events related to any medication that is used during the study that prevents the continuation of the protocolThe patient voluntarily decides to leave the study or withdraws informed consentAny adverse clinical event that requires withdrawal from the study in the opinion of the researcherCompletion of the study

Patients who have to withdraw from the study because of these criteria will not be replaced by other patients. From the moment at which the withdrawal from the trial is decided, study samples of inflammatory markers will no longer be obtained. These patients will be followed by the members of the research team in the same way as patients who complete the study until hospital discharge, guaranteeing them the same healthcare. In these cases, only safety data (serious adverse events) will be collected for the study. For patients who withdraw their consent, no further patient data will be collected in association with the trial from the moment they inform the research team.

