#### Outcomes

##### Primary outcome

The primary outcome is the proportion of patients included in the different scales of the Clavien–Dindo (C–D) classification [20] in the three groups of patients. The greater the intensity of the treatment that is necessary to correct any postoperative complication, the higher the C–D classification will be considered. Any deviation from a normal postoperative course will be classified into grade I, II (minor complications), IIIa, IIIb, IVa, IVb, and V (major complications) of this classification (Appendix 1).

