◦ Wound infection: Infection of the incisional surgical site, purulent drainage and/or isolation of pathogenic microorganisms◦ Prolonged air leak: Air escape through the thoracic drainage tubes beyond postoperative day 5◦ Bleeding: A surgical wound that requires re-intervention or the patient requires transfusion of blood products◦ Subcutaneous emphysema: Palpation of subcutaneous crepitation or the presence of subcutaneous air in a thoracic image (chest X-ray or computed tomography)◦ Bronchopleural fistula: Communication of the bronchus with the pleural space as shown on a thoracic image◦ Pleural empyema: Pleural effusion with the macroscopic presence of pus, a positive Gram stain or culture of pleural fluid, or a pleural fluid pH under 7.2 with normal peripheral blood pH◦ Cardiac herniation: Presence of the heart outside its expected position, as shown on a thoracic image◦ Surgical re-intervention: Patient who requires reoperation for any reason (pulmonary or not)Incidence of postoperative cardiac complications within 30 days postoperatively, if any of the following cardiac events occur:
◦ Cardiac arrhythmias: defined as evidence of an abnormal heart rhythm electrocardiograph (ECG) that was not present before the intervention◦ Stroke episodes: defined as an acute focal injury of the central nervous system that has a vascular cause (embolic, thrombotic or hemorrhagic) with residual motor deficit, sensory, or cognitive dysfunction◦ Cardiac failure: The presence of new respiratory distress, S3, jugular venous distension, and a new chest X-ray finding of pulmonary vascular redistribution or interstitial◦ Myocardial ischemia: An increase in ultrasensitive troponin with at least one value above the 99th percentile of the upper reference limit and at least one of the following criteria: ECG changes compared to preoperative ECG that suggests ischemia or new echocardiographic (wall motion) abnormalities◦ Cardiac arrestIncidence of postoperative renal complications.Postoperative acute kidney failure is defined as an increase of serum creatinine more than 1.5 times or ≥ 0.3 mg/dL from baseline or urine output < 0.5 mL/kg/h for 6 h using the acute kidney injury network (AKIN) classification [22]. Time frame: up to 30 days after intervention.Length of stay in the hospital and PACUUnplanned readmissions to the hospital and PACU during the first 30 postoperative days

Secondary laboratory outcomes:

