#### Statistical analysis

Descriptive statistics (mean (standard deviation; SD) or median (IQ25–75)) will be used for continuous variables. Normality will be assessed using the Kolmogorov–Smirnov test. When the variables have a normal distribution, ANOVA and a post hoc Bonferroni test will be applied. If the variables do not have a normal distribution, a non-parametric test will be used to compare them. In this case, the Kruskal–Wallis test and Mann–Whitney test will be used to make post hoc comparisons.

A one-way repeated-measures ANOVA will be performed to analyze repeated measurements of continuous variables. Categorical variables will be presented as absolute frequencies and percentages and compared between groups using the Pearson chi-squared test or Fisher exact test. The odds ratio will be calculated with the 95% confidence interval for categorical postoperative outcome variables. The statistical analyses will be performed using SPSS version 21.0. Statistical significance is set at *p* < 0.05.

Before the digitization and statistical analyses, an investigator will review the data record form for completeness and correctness. At this time, missing data will be identified, drawn from source data, and filled into the case record forms if possible. We do not expect to obtain missing data with outcome variables because they are recorded in a mandatory manner in the electronic hospital files. However, missing pre- or intraoperative data will be treated with a regression imputation method. Data will be analyzed according to the intention-to-treat principle.

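### Patients withdrawn after randomisation contribute only serious adverse events, so they cannot be placed on the full Clavien-Dindo scale, which contradicts the stated intention-to-treat analysis

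*Protocol article*

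**What the plan says.** **Withdrawal (Data collection and management).** Besides the patient's own decision to leave, the criteria include intraoperative transfusion, one-lung ventilation shorter than 60 minutes, an adverse event of a trial medication that prevents continuation, any adverse event that in the researcher's opinion requires withdrawal, and medical reasons that prevent the procedures being followed. Such patients "will not be replaced by other patients", and biomarker sampling stops. On follow-up: "These patients will be followed by the members of the research team in the same way as patients who complete the study until hospital discharge". The stated purpose is equal healthcare, and the next sentence limits the trial data: "In these cases, only safety data (serious adverse events) will be collected for the study". Consent withdrawal has its own rule: "For patients who withdraw their consent, no further patient data will be collected in association with the trial".

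**Primary outcome.** "The primary outcome is the proportion of patients included in the different scales of the Clavien–Dindo (C–D) classification". The scale runs from grade I to grade V. Under Adjudicating outcome variables, two teams assign the grade at hospital discharge.

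**Statistical analysis.** "Data will be analyzed according to the intention-to-treat principle". Also: "We do not expect to obtain missing data with outcome variables", because outcomes are recorded compulsorily in the hospital's electronic files. Imputation is described only for pre- and intraoperative data.

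**Power calculation.** 48 patients per group, raised for 5% losses to 153 in total.

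**The concern.** An intention-to-treat comparison needs an outcome for each randomised patient, or at least an attempt to obtain one. Here the protocol tells the team not to collect the primary outcome for a group defined by what happened after allocation. A separate analysis plan could not repair this, because it cannot analyse data that the protocol says are not collected.

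At stake is the basis of the primary comparison. Leaving out patients because of post-randomisation events means that the remaining groups are no longer the groups that were randomised. If the chance of withdrawal depends on the infusion received and is also related to the postoperative course, the Clavien-Dindo comparison is biased, and a larger sample does not remove that bias.

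**Working it through.** **1. Order of events.** The medication is prepared according to the allocation, and the infusions start once the paravertebral catheter is in place. Intraoperative transfusion and the length of one-lung ventilation are known only later, and the Clavien-Dindo grade is assigned later still, at discharge. A patient withdrawn during surgery therefore leaves before any grade exists.

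**2. What serious adverse events alone can show.** The article does not define a serious adverse event. On its ordinary meaning (an assumption), set against the grade definitions in Appendix 1:

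| True course | Identifiable from serious adverse events alone? |
|---|---|
| No complication | No; looks the same as grade I |
| Grade I (no treatment needed) | No |
| Grade II (drug treatment or minor intervention) | Mostly no |
| Grade III (surgical, radiologic or endoscopic intervention) | In part |
| Grade IV (intensive care, life support) | Probably |
| Grade V (death) | Yes |

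A withdrawn patient with no serious event could be uncomplicated, grade I, grade II or possibly grade III. Scoring all of these as uncomplicated would misclassify some of them; leaving them out gives a restricted comparison.

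**3. The plan's own sample size.** Inputs from Power calculation: SD 1.5, difference 1, two-sided alpha 5%, power 90%.

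- n per group = 2 × SD² × (z₀.₉₇₅ + z₀.₉₀)² / difference² = 2 × 2.25 × (1.960 + 1.282)² = 47.3, so 48.
- With 5% losses: 48 / 0.95 = 50.5, so 51 per group, and 3 × 51 = 153.

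The stated figures reproduce. Allowing for 5% losses also sits awkwardly beside expecting no missing outcomes.

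**4. Illustration of bias.** Let w be the proportion withdrawn in an arm and g the mean excess grade of withdrawn patients over completers, taken as equal in both arms. The arm's full mean is the completers' mean plus w × g, so the completers' mean is too low by w × g. With no true difference, the completers' comparison is shifted by (w₂ − w₁) × g in favour of the arm with more withdrawals.

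- Assumed w of 5% and 15% (51 × 0.05 = 2.6 and 51 × 0.15 = 7.7 patients), g = 1: (0.15 − 0.05) × 1 = 0.10 unit.
- Same rates, g = 2: 0.10 × 2 = 0.20 unit.
- Milder assumption, 0% and 5%, g = 1 to 2: 0.05 to 0.10 unit.

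Against the 1-unit target these are shifts of 5% to 20%. Neither the withdrawal rates by arm nor g is given in the protocol, and g could be negative for some triggers.

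**5. Power.** By normal approximation with 51 × (1 − loss) graded per group: 92.0% with no loss, 90.7% at 5%, 89.1% at 10% and 85.3% at 20%. Losses above 5% are assumed.

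**The case against.** The strongest reply is that nothing is really lost. These patients are followed like the others to discharge, which is when the grade is assigned, and the outcomes are in the hospital files. That stands as far as the data existing is concerned, so it would be wrong to say that the grade is irretrievable. But the follow-up is described as healthcare, and the sentence after it limits what is collected for the study. Follow-up to discharge also stops short of the 30-day time frame of several secondary outcomes. Consent does not explain the limit, since it has its own rule.

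A second reply is that withdrawal need not differ by arm. The treating physicians are blinded, and transfusion and short one-lung ventilation plausibly depend mostly on the operation. This also has force. The concern about dependence on the infusion rests mainly on the drug-related and investigator-judged adverse events.

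A reader might go further in three ways that the protocol does not support:

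- *That the worst courses are removed.* Serious events are the one thing still collected, so the highest grades would probably be seen. Short one-lung ventilation may even mark simpler surgery.
- *That the transfusion trigger is itself an outcome event.* The definition reads "Bleeding: A surgical wound that requires re-intervention or the patient requires transfusion of blood products", but it stands in a list of postoperative complications, whereas the trigger is intraoperative. Such a transfusion may be prognostic without being that outcome.
- *That power is materially reduced.* Even an assumed 20% loss leaves about 85%.

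**Conclusion.** The contradiction is real and concerns the primary outcome. Serious-adverse-event-only collection after withdrawal is incompatible with intention-to-treat analysis and with expecting complete outcomes, and no other part of the article reconciles them. Followed as written, the plan gives an incomplete primary comparison, conditioned on post-randomisation events.

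The direction and size of any bias cannot be determined from the protocol, whose only loss figure is 5% overall. The 0.1 to 0.2 unit shift shows what assumed rates of 5% and 15% and a 1-to-2-grade excess would produce; it is not an estimate. The case for changing the text rests on the contradiction, not on that figure. The sample size calculation itself is not in question.

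**What to change.** Replace the serious-adverse-event-only sentence so that stopping study drug or biomarker sampling does not end outcome collection. Suggested wording: *Every randomised patient who has not withdrawn consent will have the Clavien-Dindo grade recorded at hospital discharge and the 30-day outcomes recorded from the hospital record and the scheduled day-30 visit, and will be analysed in the allocated group.* The clinical reasons for stopping study drug need not change, and the separate rule for consent withdrawal can stay.

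The cost is modest but goes a little beyond wording. Recruitment began in January 2019, so this is an amendment to a running trial, to be communicated to the health authority as the Monitoring section requires for important modifications. It also adds some recording for withdrawn patients, chiefly between discharge and day 30. The discharge grade should need little extra work, since these patients are already followed to that point.

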### Monitoring

The inclusion of each individual patient in the study is indicated in the electronic hospital information system, and this is, thus, visible to all physicians and nurses involved in the care of the patient. This facilitates the reporting of adverse events to the principal investigator. The principal investigator will report suspected unexpected serious adverse reactions to the federal health authorities.

An external independent CRO will monitor the trial. It will verify the correct completion of data files, correct manipulation of the samples, compliance with local data protection laws, and personal confidentiality. The CRO will follow up the study each week from the beginning of recruitment until the last patient is enrolled. An inspector will be allowed to visit all the center’s facilities to evaluate the data as well as the quality and integrity of the study. At the center, the study files will be reviewed and compared directly with the source documents. The inspector will also discuss the development of the study with the researcher and will verify that the facilities are still acceptable. Only two members of the research group will have access to the identification codes corresponding to the personal data of the patients included in the trial. All important protocol modifications will be communicated to AEMPS (Spanish health authorities).

### Access to data and dissemination policy

The study data will be kept in a locked cupboard, and only members of the research team and the external CRO will be able to access the database. The results of the study will be made public through publication in scientific journals and conferences related to anesthesia in thoracic surgery, as well as through the platform of ClinicalTrials.org.

### Power calculation

The primary outcome of this clinical trial is the comparison of the proportion of patients included in the different C–D classifications, which indicate the severity of postoperative complications for thoracic surgery. Two comparisons are planned: IV lidocaine + SS-PV vs remifentanyl IV+ SS-PV, and lidocaine PV + SS-IV vs remifentanyl IV+ SS-PV. The sample size is calculated based on the C–D classification ordinal scale. According to a similar study design by our research group, the standard deviation of this scale is approximately 1.5 units. Thus, it is necessary to include 48 patients per group with an alpha risk of 5% and a beta risk of 10% in a two-tailed comparison to detect differences ≥ 1 unit. Because losses are estimated to be 5%, the final sample size should be at least 153 patients (sample size calculator GRANMO version 7.12 April 2012).

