### Randomization

Patients will be randomized into the following three groups (1:1:1 ratio): intravenous lidocaine and PV saline (group 1); IV and PV saline solution with lidocaine (group 2); or IV remifentanyl and PV saline solution (group 3). The randomization will be performed using the software EPIDAT 3.1 before the first patient is recruited, and the randomization codes will be kept in a sealed envelope with a number on the outside of the envelope.

A study nurse will be in charge of preparing the medication according to the result obtained in the envelope. The surgical anesthesiologist will receive the assigned and prepared medication for the corresponding group with only the identification of IV perfusion (500 mL) and PV perfusion (100 mL) without knowledge of the group to which the patient belongs. The content of solutions will be indistinguishable to the investigating team because all of the solutions are clear liquids.

For bias control, the physicians involved will be blinded to the techniques used, including the anesthesiologist responsible for the intraoperative management of the patient, the physician responsible for postoperative control in the postoperative care unit, and the guard physician who will perform the cognitive dysfunction test preoperatively and postoperatively, as well as the follow up until the month of surgery. Those responsible for analysis of the biological samples will also be blinded.

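### The 48 per group gives 90% power only for a single uncorrected 5% test, while two primary comparisons are planned and the multiplicity rule changes with a normality pre-test; with family-wise error held at 5%, power per comparison is about 80–86%

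*Protocol article*

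**What the plan says.** In the protocol article, the Power calculation section sets out the primary analysis as pairwise: "Two comparisons are planned", IV lidocaine against remifentanil and paravertebral lidocaine against remifentanil. It treats the Clavien–Dindo grade as a numerical scale, on which "the standard deviation of this scale is approximately 1.5 units", and asks for "48 patients per group with an alpha risk of 5% and a beta risk of 10% in a two-tailed comparison". The target difference is 1 unit on that scale. With 5% losses the total is 153, allocated 1:1:1. No allowance for two comparisons is mentioned.

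The Statistical analysis section gives rules by type of variable, with significance at p < 0.05 throughout:

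- Normally distributed: "ANOVA and a post hoc Bonferroni test will be applied". It does not say whether Bonferroni covers two pairs or three.
- Not normally distributed: "the Kruskal–Wallis test and Mann–Whitney test will be used to make post hoc comparisons". No adjustment is stated, nor whether the pairwise tests depend on the overall test.
- Categorical: Pearson chi-squared or Fisher, with no pairwise rule.

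A Kolmogorov–Smirnov test decides between the first two. The section does not say which branch the Clavien–Dindo outcome takes.

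**The concern.** The sample size and the analysis rest on different error rules. The sizing spends the full 5% on each of two comparisons that share a control arm. The analysis applies Bonferroni in one branch and relies on an overall test, whose role is not spelled out, in the other. The trial data select the branch.

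Two things are at stake for the primary outcome. First, the stated 90% power may not be what any error-controlling route delivers. Second, a pairwise p-value has no fixed meaning. An unadjusted p of 0.03 is positive as a Mann–Whitney result at 5% (given a significant Kruskal–Wallis test, if that is required). Under Bonferroni it becomes 2 × 0.03 = 0.06 for two comparisons or 3 × 0.03 = 0.09 for three pairs, and is negative in both cases.

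**Working it through.** **Inputs (Power calculation section).** Difference 1 unit, SD 1.5, two-sided alpha 0.05, power 0.90, 5% losses, two comparisons with a shared control. The grade is treated as normal, as the protocol does.

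**1. Reproduce the plan's figure.** n per group = 2 × (z₁₋α/₂ + z₀.₉₀)² × SD² / difference².

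- 2 × (1.960 + 1.2816)² × 2.25 = 47.3, so 48 per group.
- 48 / 0.95 = 50.5, so 51 per group, and 3 × 51 = 153.

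Both stated figures reproduce, but only at an uncorrected two-sided 5% for one comparison.

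**2. Power at 48 per group under Bonferroni.** The standardised difference is 1 / (1.5 × √(2/48)) = 3.266, and power ≈ Φ(3.266 − z₁₋α/₂).

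| Rule | alpha | z | Power (normal) | Power (t-test) | n per group for 90% |
|---|---|---|---|---|---|
| Uncorrected | 0.05 | 1.960 | 90.4% | 89.8% | 48 |
| Bonferroni, two comparisons | 0.025 | 2.241 | 84.7% | 83.7% | 56 |
| Bonferroni, three pairs | 0.0167 | 2.394 | 80.8% | 79.4% | 61 |

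If no patient is lost (51 per group), the two Bonferroni rows rise only to 87.0% and 83.5% (normal), so the allowance for losses does not restore 90%.

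**3. Power with Kruskal–Wallis as a gate.** Simulated normal data, SD 1.5, 48 per group, Kruskal–Wallis at 5%, then Mann–Whitney at 5% against remifentanil. A comparison counts as a success only if both tests reject.

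- Both lidocaine arms differ from remifentanil by 1 unit: about 85–86% per comparison, about 80% for both together.
- Only one lidocaine arm differs: about 86% for that arm.
- One arm differs by 1 and the other by 0.5: about 80% for the first (79% to 81% across runs).
- Mann–Whitney alone, without the gate: about 88%.

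The same calculation with normal-theory tests gives about 88%, 88% and 84% for the first arm in the three scenarios, so the gate leaves power below 90% there too.

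**4. Family-wise error.**

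- Two ungated tests at 5% with a shared control (correlation 0.5): 9.1%. If independent it would be 1 − 0.95² = 9.75%.
- Gated, all three groups equal: 4.2% for the two comparisons, and 5.0% if all three pairs are tested.
- Gated, one lidocaine arm effective and the other equal to remifentanil: at most about 5%.

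The gate works for three groups for a simple reason. If all three are equal, no false positive can occur unless the overall test rejects, which happens 5% of the time. If only two are equal, there is just one true pairwise null hypothesis, and it is tested at 5%.

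**The case against.** The strongest reply is that the rank branch is not unprotected. It names Kruskal–Wallis and calls the Mann–Whitney tests post hoc, which ordinarily means after a significant overall test. With three groups that holds the family-wise error near 5%. The Bonferroni rule is written for normally distributed variables, and an ordinal grade is more likely to fall in the rank branch. Detailed multiplicity rules may also be left to an analysis plan that is not shown.

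Most of this stands. A reader might infer that the rank branch has no error control and that the trial therefore runs a 9% false-positive risk. The documents do not support that: 9% needs the two comparisons to be run without the overall test, and the protocol does not say they will be. It does leave that reading open, because the Power calculation section describes as planned the same comparisons that the Statistical analysis section would treat as post hoc.

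A reader might also infer that the gate costs nothing, because Kruskal–Wallis itself rejects in about 91–92% of trials when one or both lidocaine arms differ by 1 unit. That is the power of the overall test, not of a comparison with remifentanil. Requiring a second test can only lower the power of that comparison, here from about 88% to about 85–86%.

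The appeal to an analysis plan does not remove the point. The article itself states the alpha, the number of comparisons and the post hoc rule for each branch, and these do not fit together.

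**Conclusion.** The point holds as a mismatch between sizing and analysis, together with a primary decision rule that is not fixed in advance. The 48 per group and 153 in total are arithmetically right for one uncorrected comparison. No route that controls the family-wise error at 5% was found to give the stated 90% per comparison at that size: the range is 79–85% with Bonferroni and about 80–86% with the gate. The risk of missing a true 1-unit difference is therefore about 14–21%, not 10%. The family-wise error is about 4–5% if the gate is applied, and about 9% only on the ungated, uncorrected reading.

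These figures rest on the protocol's SD of 1.5, its 1-unit difference, a roughly normal grade and 48 evaluable patients per group. They do not show that the trial is too small to run. They show that its stated power is too favourable, and that the test and error rule behind its primary conclusion depend on a pre-test of the data.

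**What to change.** For the Clavien–Dindo outcome:

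1. Drop the normality pre-test.
2. State that the three-group Kruskal–Wallis test at two-sided 5% is a formal gate. Only if it is significant is each lidocaine arm compared with remifentanil by Mann–Whitney at 5%, with no further correction.
3. Restate the power as about 80–86% per comparison at 48 per group, the lower end applying if the other lidocaine arm lies midway.

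If Bonferroni is preferred, name the number of comparisons and restate the power as 84–85% (two) or 79–81% (three pairs).

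The change takes a few sentences, should be made before unblinding, and adds no patients. Its cost is a less favourable stated power. Keeping 90% under Bonferroni would instead need 56 per group for two comparisons (59 with 5% losses, 177 in total) or 61 for three pairs (65 with losses, 195 in total).
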